## Abstract

**Background:**

Surgical site infections (SSIs) cause significant patient suffering. Surveillance and feedback of SSI rates is an evidence-based strategy to reduce SSIs, but traditional surveillance methods are slow and prone to bias. The objective of this cluster randomized controlled trial (RCT) is to determine if using optimized statistical process control (SPC) charts for SSI surveillance and feedback lead to a reduction in SSI rates compared to traditional surveillance.

**Methods:**

The Early 2RIS Trial is a prospective, multicenter cluster RCT using a stepped wedge design. The trial will be performed in 29 hospitals in the Duke Infection Control Outreach Network (DICON) and 105 clusters over 4 years, from March 2016 through February 2020; year one represents a baseline period; thereafter, 8–9 clusters will be randomized to intervention every 3 months over a 3-year period using a stepped wedge randomization design. All patients who undergo one of 13 targeted procedures at study hospitals will be included in the analysis; these procedures will be included in one of six clusters: cardiac, orthopedic, gastrointestinal, OB-GYN, vascular, and spinal. All clusters will undergo traditional surveillance for SSIs; once randomized to intervention, clusters will also undergo surveillance and feedback using optimized SPC charts. Feedback on surveillance data will be provided to all clusters, regardless of allocation or type of surveillance. The primary endpoint is the difference in rates of SSI between the SPC intervention compared to traditional surveillance and feedback alone.

**Discussion:**

The traditional approach for SSI surveillance and feedback has several major deficiencies because SSIs are rare events. First, traditional statistical methods require aggregation of measurements over time, which delays analysis until enough data accumulate. Second, traditional statistical tests and resulting *p* values are difficult to interpret. Third, analyses based on average SSI rates during predefined time periods have limited ability to rapidly identify important, real-time trends. Thus, standard analytic methods that compare average SSI rates between arbitrarily designated time intervals may not identify an important SSI rate increase on time unless the “signal” is very strong. Therefore, novel strategies for early identification and investigation of SSI rate increases are needed to decrease SSI rates. While SPC charts are used throughout industry and healthcare to improve and optimize processes, including other types of healthcare-associated infections, they have not been evaluated as a tool for SSI surveillance and feedback in a randomized trial.

**Trial registration:**

ClinicalTrials.govNCT03075813, Registered March 9, 2017.

## Administrative information

Note: the numbers in curly brackets in this protocol refer to SPIRIT checklist item numbers. The order of the items has been modified to group similar items (see http://www.equator-network.org/reporting-guidelines/spirit-2727-statement-defining-standard-protocol-items-for-clinical-trials/__;!!OToaGQ!_EXmkNIa7FXJ6Jgpz6jAg0-5b4y1YtykPoGvMbNiq-XcNuK6n1xNKyptp7XW0y93TTg95kA$).

## Introduction

### Background and rationale {6a}

Surgical site infections (SSIs) are the most common and costly healthcare-associated infections (HAIs) in the USA [1–4]. More than 150,000 patients acquire a SSI each year and suffer from adverse outcomes, including longer hospitalizations and increased mortality than patients without SSIs [5–7]. In total, SSIs cost the US healthcare system more than $3 billion annually [4, 8]. Over the past decade, hospitals across the USA have spent considerable time and resources optimizing SSI prevention processes. While most hospitals have greatly improved compliance with important process measures, improved process performance has not led to decreased rates of SSI [9, 10]. As a result, innovative strategies to prevent SSIs are greatly needed.

Statistical process control (SPC) is an analytic approach that combines time series analysis methods with graphical presentation of data to determine whether a process or rate exhibits “common cause” natural variation or “special cause” variation due to circumstances that have not previously been inherent in the process [11]. In other words, SPC methods help separate “noise” from a true signal. Commonly employed in manufacturing and other industries, SPC methods have emerged as useful tools for identifying and analyzing changes in HAI rates [12–15]. To date, however, SPC methods are not commonly utilized in a rigorous manner to provide real-time surveillance of HAIs such as SSIs.

Feedback of SSI data to surgical personnel is a cornerstone of SSI prevention [16] and is well proven to lead to lower rates of SSI [17–20]. Indeed, the feedback of surveillance data to surgeons has repeatedly been shown to improve surgical patient outcomes, including SSI [17–20]. However, current surveillance and feedback strategies are significantly limited. SPC surveillance and feedback of SSI data can overcome these limitations and decrease rates of SSI. SPC surveillance is designed to rapidly identify important increases in the rate and occurrence of SSIs. When a signal is identified, an investigation can be performed to provide rapid review and feedback to determine if process changes are required, potentially reducing the risk of SSI for subsequent patients.

## Objectives {7}

To measure the effectiveness of surveillance using optimized SPC methods and feedback on rates of SSI compared to traditional infection surveillance methods and feedback.

### Primary objective

To determine if hospital clusters randomized to SSI surveillance with optimized SPC methods and feedback collectively have lower rates of SSI compared to hospital clusters randomized to traditional SSI surveillance methods and feedback.

### Secondary objectives

To determine if hospital clusters randomized to SSI surveillance with optimized SPC methods and feedback collectively have lower rates of superficial-incisional, deep-incisional, organ/space, and/or complex SSI compared to hospital clusters randomized to traditional SSI surveillance methods and feedback.To determine and compare the number of signals identified using optimized SPC methods and traditional surveillance methods over the 3-year post-baseline period.
Descriptive – overall numbers; then summarize per cluster per monthFor comparison – develop standardized rate, likely number of signals per 100 procedures performedTo estimate and compare the proportion of signals that led to investigations using optimized SPC methods versus traditional surveillance methods, including the number of true positive signals, false positive signals, positive predictive value, sensitivity, and specificity of each method.To summarize the preventability score for SSIs reviewed during the study and compare between treatment arms.To compare the timing of true positive signal identification between the two surveillance strategies.
Average time between signalsProportion of true positive signals in which optimized SPC methods found the signal first.

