### Intervention description {11a}

Data entered locally by infection preventionists at DICON hospitals are transmitted to the DICON Surgical Database per routine practices. Data submitted to the DICON Surgical Database will undergo scheduled weekly analysis by optimized SPC methods. If a signal is generated, study personnel in DICON will be notified to adjudicate the signal and determine if further action is required.

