### Outcomes {12}

Primary endpoint (domain: healthcare-associated infection):
Specific measurement – SSI rate, calculated as the number of SSIs per 100 proceduresSpecific metric – Differences in the rates of SSI between the intervention compared to traditional surveillance and feedback alone
SSIs will be defined using standard NHSN definitions
i.DICON personnel train local infection preventionists about how to use and interpret SSI definitions. Thus, standard definitions and methods will be used at all study hospitalsCluster-level risk adjustment will be performed using median surgical volume [25] and median NHSN Risk Index (an operation- and patient-specific risk score that predicts SSI) [26, 27] per clusterMethod of aggregation – Mean rates will be summarized for each cluster for each 3-month study “step”

Secondary endpoints:
Several secondary outcomes will be compared between clusters receiving intervention and clusters receiving traditional surveillance and feedback
Stratified analysis of primary outcome – SSI rates stratified by type of SSI (superficial-incisional, deep-incisional, or organ/space).Descriptive outcomes
◦ Description of and difference in number and type of signals◦ Difference in number of investigations of increased rates of SSI◦ Total number and differences in proportion of signals that led to investigations◦ Proportion of SSIs determined to be potentially preventable, based on preventability score◦ Timing of signals

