**Fig. 2 Fig2:**
[figure not shown]
Schematic for stepped wedge design for the Early Recognition and Response to Increases in Surgical Site Infection (Early 2RIS) Trial. Gray = control, during which hospitals will receive traditional SSI surveillance, including biannual data reports. Any signals identified in biannual reports or detected by local personnel will undergo further investigation. White = intervention, during which hospital clusters will receive feedback from traditional surveillance and signals generated by applying optimized SPC methods to SSI surveillance data

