## Assignment of interventions: blinding

### Who will be blinded {17a}

SSI signals prospectively identified using optimized SPC methods during the intervention period will undergo blinded review to ensure that signal adjudication occurs without knowledge of which hospital cluster generated the signal. Following review, the study coordinator will unblind the signal, and, if the hospital cluster is randomized to intervention, the study team will proceed with the actions required to appropriately respond to the identified increase in SSIs. If the hospital cluster is a control cluster, then the study coordinator will document the signal, but no further action will be taken.

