## Data collection and management

### Plans for assessment and collection of outcomes {18a}

Routine data on surgical procedures and SSIs will be collected via a standardized limited dataset, per routine DICON practices (Table 2) [28]. No identifiable patient or surgeon data are transmitted to the DICON Surgical Database.

**Table 2 Tab2:** Variables in the DICON Surgical database

All surgical patients	Hospital
	Type of procedure
	Patient identifier
	Date of procedure
	Age
	Sex
	Surgeon identifier
	Start/stop times
	ASA score
	Wound class
	Risk index
	SSI (yes/no)
Patients with Infection	Date of infection
	Type of SSI
	Location at diagnosis
	Organism

When a signal is identified, data will be collected on the rationale for signal adjudication (action vs. no action). If a signal requires action, additional data will be collected for further investigation, per routine protocol.

The majority of data collection will occur through methods already developed and utilized by study hospitals. In brief, each hospital routinely submits limited datasets to the DICON Surgical Surveillance Database, including all variables listed in Table 2. Data definitions and data collection methods are standardized across DICON hospitals. Following signal adjudication, additional data will be collected in a REDCap database to document actions and rationale.

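### The between-arm comparison of preventability among reviewed SSIs cannot be separated from the arms' different routes to review

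*Protocol article*

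**What the plan says.** The protocol article, under Secondary objectives, sets the aim "To summarize the preventability score for SSIs reviewed during the study and compare between treatment arms". This names both the subset (reviewed SSIs) and the contrast (between arms).

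Outcomes {12} opens its secondary endpoints with "Several secondary outcomes will be compared between clusters receiving intervention and clusters receiving traditional surveillance and feedback". Under the descriptive outcomes it then lists "Proportion of SSIs determined to be potentially preventable, based on preventability score", without saying that only reviewed SSIs are counted.

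The routes to review are given in four places:

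- The Fig. 2 legend, control phase: "Any signals identified in biannual reports or detected by local personnel will undergo further investigation".
- The same legend, intervention phase: "hospital clusters will receive feedback from traditional surveillance and signals generated by applying optimized SPC methods to SSI surveillance data".
- Intervention description {11a}: "Data submitted to the DICON Surgical Database will undergo scheduled weekly analysis by optimized SPC methods". Study personnel then adjudicate any signal.
- Who will be blinded {17a}, on an SPC signal after blinded adjudication: "If the hospital cluster is a control cluster, then the study coordinator will document the signal, but no further action will be taken".

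Plans for assessment and collection of outcomes {18a} says when case-level information is gathered: "If a signal requires action, additional data will be collected for further investigation, per routine protocol".

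The Secondary analyses section assigns models or tests to several outcomes. Preventability is not among them, so it falls under the remaining outcomes, which are only to be summarized.

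**The concern.** An SSI can contribute to this comparison only if it is reviewed. Review comes after randomization, and the intervention is designed to change when and where it happens. Randomization therefore does not make the reviewed SSIs in the two phases comparable, even though it does so for all SSIs.

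Two phases with the same true share of preventable SSIs could show different proportions because one phase reviews more SSIs, or SSIs from a different mix of true and false rate increases. A lower proportion under SPC could be taken as a sign that avoidable infections had been removed, and a higher one as a sign that SPC finds more avoidable infections. The planned data cannot tell either reading from a change in selection.

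**Working it through.** **Side by side.** The article gives no planned figure for this outcome, so there is none to reproduce. The first step is to set out what leads to review in each phase.

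| Trigger | Control phase | Intervention phase |
|---|---|---|
| Biannual-report or locally detected signal | Investigated | Investigated |
| SPC signal, after adjudication | Documented, no action | Acted on if adjudication requires it |

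Nothing in the article provides for scoring all SSIs, a random sample of them, or the SSIs behind SPC signals in control clusters.

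**Illustration with no true difference.** Every SSI has the same chance of being preventable in both phases, and only the trigger differs.

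Inputs from the article (Explanation for the choice of comparators {6b}):

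- SPC sensitivity 0.88 and specificity 0.75 (validation data)
- traditional sensitivity 0.33 to 0.65

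Inputs assumed, because the article does not give them:

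- traditional specificity 0.75, 0.90 or 0.98
- a true rate increase in a fraction p = 5%, 10% or 20% of cluster-periods
- a 1.5-fold SSI rate in those periods
- preventable share 0.50 in those periods and 0.25 otherwise
- SPC and traditional signals independent of each other

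Formulas:

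- w1 = p × 1.5 × sensitivity; w0 = (1 − p) × (1 − specificity)
- share preventable among reviewed = (0.50 × w1 + 0.25 × w0) / (w1 + w0)
- fraction of SSIs reviewed = (w1 + w0) / (1.5p + 1 − p)
- intervention phase, either signal: sensitivity = 1 − (1 − traditional sensitivity) × 0.12; specificity = traditional specificity × SPC specificity

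One case in full: p = 0.10, traditional sensitivity 0.65, traditional specificity 0.90.

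- Control: w1 = 0.0975, w0 = 0.0900. Share = 0.07125 / 0.1875 = 38.0%. Reviewed = 0.1875 / 1.05 = 17.9%.
- Intervention, before adjudication: sensitivity 0.958, specificity 0.675, w1 = 0.1437, w0 = 0.2925. Share = 0.144975 / 0.4362 = 33.2%. Reviewed = 0.4362 / 1.05 = 41.5%.
- Difference, intervention minus control: −4.8 points, from selection alone.

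Over all 18 combinations the difference runs from −12.4 to +2.7 points. The fraction reviewed is 4% to 36% in control and 31% to 58% in intervention.

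**Allowing for adjudication.** SPC signals reach investigation only after adjudication. Suppose it keeps all true signals and removes 60% or 80% of false ones, so that SPC specificity becomes 0.90 or 0.95. Both percentages are assumptions. In the case above:

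- 60% removed: w0 = 0.9 × (1 − 0.81) = 0.1710. Share = 0.1146 / 0.3147 = 36.4%, difference −1.6 points.
- 80% removed: w0 = 0.9 × (1 − 0.855) = 0.1305. Share = 0.104475 / 0.2742 = 38.1%, difference +0.1 points.

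Over the same 18 combinations the ranges become −8.2 to +4.6 points (60%) and −4.9 to +5.4 points (80%).

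**Case with no artefact.** If the preventable share is the same inside and outside true increases, the formula returns that share in both phases and the difference is zero.

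**The case against.** The strongest reply is that this is a descriptive process measure. Outcomes {12} files it under descriptive outcomes, and no test is planned. The objective openly conditions on reviewed SSIs, and changing which SSIs come to review is part of what SPC surveillance does. Describing what each strategy's reviews turn up is legitimate. All of this stands, and it limits the point to interpretation. It does not remove the problem, because the objective still asks for a comparison between treatment arms and the article nowhere says that this is not a treatment effect.

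It can also be said that the article does not define reviewed, and that other control-phase SSIs might be reviewed too. That is possible. The reading used here is an inference from the data-collection and blinding sections, and nothing in the article points the other way.

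Four stronger readings are tempting, and the document does not support them:

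- *The difference reflects selection and not the intervention.* This is too absolute. It would mix the two in unknown proportions.
- *Those who score know the phase and the trigger.* The blinding section covers signal adjudication and the response to a signal. The article does not say who assigns the score, when, or with what information.
- *The bias has a predictable size and direction.* It does not, because traditional specificity, the effect of adjudication and the link between preventability and signals are not stated.
- *The Outcomes label means all SSIs, so the intervention arm looks worse because more are reviewed.* That requires unscored SSIs to be counted as not preventable, which no section says. The label refers to the score, so it can be read as scored SSIs only.

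**Conclusion.** The point holds in this form: as the article describes review, a between-arm difference in the proportion preventable among reviewed SSIs cannot be separated from the difference in which SSIs each phase reviews. It rests on case-level review following signals that require action, and on SPC signals in control clusters not being acted on.

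The possible artefact ranges from nothing to several percentage points in either direction, and about 12 points at the extreme of the assumed inputs. These figures illustrate the problem and do not estimate a bias. The primary SSI-rate analysis is unaffected. What is at stake is how one descriptive secondary outcome may be read. It is worth correcting because the remedy is small and changes what can be concluded from that outcome.

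**What to change.** 1. In Secondary objectives, remove the arm comparison for pooled reviewed SSIs, or state that it is descriptive and does not estimate an effect of the intervention.
2. Report preventability by review trigger (SPC signal, traditional signal) and by phase, each with the number of SSIs reviewed out of all SSIs in that phase.
3. In Outcomes {12}, state that the denominator is reviewed SSIs, to match the objective.

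The cost is a wording change and one extra table. The trial gives up a pooled arm contrast, but one that could not have been interpreted.

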## Trial design {8}

The Early 2RIS Trial is a prospective, multicenter cluster randomized controlled trial using stepped wedge design. Baseline data will be collected for 12 months. The active component of the trial will be performed in 29 hospitals in the Duke Infection Control Outreach Network (DICON) hospitals and 105 clusters over 3 years, from March 2017 through February 2020.

## Methods: participants, interventions, and outcomes

### Study setting {9}

All study hospitals participate in DICON (http://dicon.medicine.duke.edu/). DICON is a network of over 60 community hospitals in North Carolina, South Carolina, Georgia, Virginia, Florida, and West Virginia that provides access to consultative services from infection prevention experts, data analyses and benchmarking, and educational materials designed by faculty at the Duke University School of Medicine. Each site has a contract (Infection Prevention Program Development Services Agreement) with Duke, which includes a data use agreement (DUA) and business agreement (BAA). Routine network activities, including regular visits by DICON liaison nurses, data reports, and education, will continue throughout the study. All participating hospitals submitted letters of support for inclusion in the study.

### Eligibility criteria {10}

#### Inclusion criteria

All patients who undergo one of 13 targeted procedures at 29 study hospitals will be included in the analysis. These procedures were selected because they are frequently performed in community hospitals and/or are associated with particularly adverse outcomes if complicated by SSI. Eligible procedures will be categorized by type at each hospital using ICD10 codes published by the US CDC’s National Healthcare Safety Network (NHSN) [21]. Clusters will be constructed at each participating hospital based on the type of surgical procedure performed (Table 1). Clusters were constructed to ensure that surgeons who perform similar types of procedures were grouped together to limit potential bias. *These clusters will be the units for randomization and analysis*.

**Table 1 Tab1:** Procedures included in each cluster

Cluster	Procedure
Cardiac	Coronary artery bypass graft
	Cardiac valve replacement
GI	Colon
	Herniorrhaphy
Joint	Knee arthroplasty
	Hip arthroplasty
OB-GYN	Cesarean section
	Hysterectomy
	Vaginal hysterectomy
Spine	Spinal fusion
	Laminectomy
Vascular	Carotid endarterectomy
	Peripheral venous bypass

#### Exclusion criteria

DICON hospitals that did not submit a letter of support for participating in the study will be excluded. Patients not undergoing one of the 13 procedure types at the 29 study hospitals will be excluded from the analysis. Patients undergoing one of the 13 procedure types at the 29 study hospitals with infection present at the time of surgery will be excluded from the analysis.

### Who will take informed consent? {26a}

Patients will not be consented as part of this study. A waiver of informed consent was granted by the Duke University Health System IRB.

### Additional consent provisions for collection and use of participant data and biological specimens {26b}

N/A. Patients will not be consented for this trial.

